### Statistical methods

The statistical analyses will be carried out at the CIC-EC in Reunion, under SAS® (version 9.2, SAS Institute Inc., Cary, NC, USA).

Description of the initial characteristics of the screened patients and of the included patients will be done by usual statistics (number, percentage, average ± standard deviation or median and range).

Effective implementation of the SME program and the effective participation will be documented.

The assessment of efficacy of the intervention will be performed in a single analysis, according to the intention to treat principles (*i.e.* according to group allocated by randomisation) with type I error equal 5%, and bilateral formulation of Student t-test (primary analysis).

In the two compared groups, the deficient data on HbA1c (%) at two years (week 96) will be replaced by the measurement obtained at week 84.

If the primary analysis shows a significant difference between the two groups, a comparison of the mean change in HbA1c (%) S96-S0 will be done by the level of participation (secondary analysis using 1-factor ANOVA model): i) basic level ("initial structured therapeutic education only"), ii) level 1 (“structured on-going SME support” without specific additional focused sessions), iii) level 2 (“structured on-going SME support” with specific additional focused sessions).

Analysis of longitudinal data gathered during two years will used in generalised estimating equations (GEE) adapted to repeated measurements in order to test the trends described over the duration of the supervision.

Analysis of the time between randomisation and occurrence of a level of HbA1c <7% (first event observed) will be performed by the Kaplan-Meier method, with comparison of survival curves between groups by Log-rank test.

At each annual collection point the anti-diabetic treatments will be classified into four hierarchical categories: 1) non-insulin antidiabetic monotherapy, 2) non-insulin antidiabetic bi-, tri- (or more) therapy, 3) one injection of insulin, 4) two or more injections of insulin. Between two collection points, moves from one category to a higher (or lower) category will be identified as a reinforcement (or reduction) of the treatment. The interaction between the intervention and treatment category will be tested in the appropriate multivariate models (ANCOVA, GEE, time-dependent variable in the Cox model).

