**Methods/Design:**

ERMIES is a randomised controlled trial designed to test the efficacy of a long-term (2 years) structured group self management educational intervention in improving blood glucose in non-recent, insufficiently controlled diabetes. After an initial structured educational cycle carried out blind for the intervention arm, patients will be randomised in two parallel group arms of 120 subjects: structured on-going group with educational intervention maintained over two years, versus only initial education. Education sessions are organised through a regional diabetes management network, and performed by trained registered nurses at close quarters. The educational approach is theoretically based (socio-constructivism, social contextualisation, empowerment, action planning) and reproducible, thanks to curricula and handouts for educators and learners. The subjects will be recruited from five hospital outpatient settings all over Reunion Island. The main eligibility criteria include: age ≥18 years, type 2 diabetes treated for more than one year, HbA1c ≥ 7.5% for ≥3 months, without any severe evolving complication (ischaemic or proliferative retinopathy, severe renal insufficiency, coronaropathy or evolving foot lesion), and absence of any major physical or cognitive handicap. The primary outcome measure is HbA1c evolution between inclusion and 2 years. The secondary outcome measures include anthropometric indicators, blood pressure, lipids, antidiabetic medications, level of physical activity, food ingestion, quality of life, social support, anxiety, depression levels and self-efficacy. An associated nested qualitative study will be conducted with 30 to 40 subjects in order to analyse the learning and adaptation processes during the education cycles, and throughout the study.

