### Sample size consideration

The efficacy assessment is based on the following main judgement criterion: developments between inclusion (week 0) and two years (week 96) of the percentage of glycated haemoglobin HbA1c (%).

The expected benefit is a decrease at two years of at least 1% in the average HbA1c between the group “structured on-going SME support” and the control group “Initial structured education cycle only”. An absolute difference of 1% at two years between the two groups appears relevant [23,24,29,32,39,60-62].

To show an absolute difference of 1% of HbA1c, with a standard deviation of 2.5%, a type I error rate of 5% and a power of 80%, it is necessary to include 99 subjects per group in a bilateral situation.

Because of an estimated data deficiency of 20% at two years (drop out, refusals, deaths), it is planned to include 120 subjects per group, making a total of 240.

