### Randomisation methods

Block randomisation is carried out on two stratification factors: insulin treatment on inclusion (yes/no - two strata), and inclusion centre (five strata). The numbers of participants in each group are balanced with a ratio of 1:1. The 10 randomisation lists are drawn up by the statistician of the CIC-EC of Reunion before the start of the research.

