## Discussion

Available studies which were carried out on the basis of these inclusion criteria (adult diabetes patients remaining at very high risk of complications due to persistent poor blood glucose control with HbA1c in excess of 7.5%) have shown a favourable effect from educational intervention at six months and one year, but the question of the efficacy of maintenance at two years, and of intensification by means of on-going structured intervention at the proximity level, still remains unanswered as compared to a sole initial structured education.

The relatively heterogeneousness of these patients showing insufficient therapeutic control (treatment by OADs or GLP-1 analogue, basal or multi-day insulin therapy) may give rise to significant differences in metabolic control. Randomisation with stratification into two groups in accordance with the addition of insulin therapy will make it possible to balance the spread of treatments between the two arms at the time of inclusion, and to assess situations presenting comparable initial medication treatments. On the other hand, anti-diabetic treatments may mask the effects of therapeutic education on the level of blood glucose control: i.e. the drug therapy reinforcement required due to the lower efficacy of the education in one group could minimise the difference between the two intervention groups. Although that is not the case in the available studies that have assessed this issue, it appears important to record the changes of anti-diabetic treatments occurring throughout the study [22,23,39].

Maintained structured educational on-going support over two years requires co-ordination, in parallel with medical and diabetological supervision, thanks to the existence of an education coordination network in Reunion. The network has the resources and already conducts structured education cycles. Self management education sessions are carried out by trained and experienced health care professionals, with an empowerment approach. The SME style is theoretically based and reproducible, with curricula and handouts making it possible to renew educational actions on the same bases. The potential investment of peer educators or expert patients has not been retained for this ERMIES study design, since the French and Reunion context is currently not yet ready to include such issues. However, this is an important clue to evaluate and implement in the future [37-39].

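### The primary t-test is valid but unadjusted: it uses neither week-0 HbA1c as a covariate nor the two stratification factors, so it gives up precision and tends to be conservative

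*Protocol article*

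**What the plan says.** All references are to the protocol article.

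- **Primary test (Statistical methods).** One intention-to-treat analysis, "with type I error equal 5%, and bilateral formulation of Student t-test (primary analysis". No covariate or stratum is named. ANCOVA appears later in the section, only among the models for the interaction between intervention and antidiabetic treatment category.
- **Randomisation (Randomisation methods).** "Block randomisation is carried out on two stratification factors: insulin treatment on inclusion (yes/no - two strata), and inclusion centre (five strata", which makes ten lists, allocated 1:1.
- **Why insulin is a stratifier (Discussion).** Heterogeneous treatment is said to be a possible source of differences in control, and the section adds: "Randomisation with stratification into two groups in accordance with the addition of insulin therapy will make it possible to balance the spread of treatments".
- **Endpoint.** The abstract states: "The primary outcome measure is HbA1c evolution between inclusion and 2 years". The sample size section defines the criterion as "developments between inclusion (week 0) and two years (week 96) of the percentage of glycated haemoglobin HbA1c". The Statistical methods section writes the change as S96-S0 for the secondary ANOVA by level of participation.
- **Effect and SD (Sample size consideration).** "An absolute difference of 1% at two years between the two groups appears relevant"; the calculation is made "To show an absolute difference of 1% of HbA1c", and its variability is given as "with a standard deviation of 2.5"%. The text does not say whether this is the SD of the change or of the week-96 value.

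**The concern.** The design records three quantities before any outcome is known: week-0 HbA1c, insulin at inclusion and centre. The primary test models none of them.

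**Baseline.** A t-test on the change subtracts week-0 HbA1c in full, which is a regression with the baseline slope fixed at 1. Unless the true slope is 1, estimating it gives a smaller residual variance.

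**Strata.** Stratified blocks force the arms to be balanced on insulin and centre. If these predict the tested variable, the treatment difference varies less from trial to trial than an unstratified t-test assumes. The standard error is then too large, the confidence interval too wide and the type I error below the nominal 5%.

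At stake is precision in the trial's one confirmatory comparison: a real difference could be missed that the same patients and measurements would have shown. The unlabelled SD adds to this, because the power of a change-score test depends on what the 2.5% describes.

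**Working it through.** **1. Inputs.** From the sample size section: difference 1, SD 2.5, two-sided 5%, power 80%, 99 evaluable per group, 120 enrolled per group, 20% loss. Evaluable per arm after loss: 120 × 0.80 = 96. From Randomisation methods: 2 × 5 = 10 strata. Assumed, because the protocol does not give them: the correlation r between week 0 and week 96 (0.3 to 0.6, with 0.7 as a further check), equal variances at the two visits, and the strata R².

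**2. The plan's own figure.** n = 2 × (1.96 + 0.842)² × 2.5² / 1² = 98.1, rounded up to 99 per group. The stated 99 reproduces. At 96 per arm, power = Φ(1 / (2.5 × √(2/96)) − 1.96) = Φ(2.771 − 1.96) = 79.1%. The noncentral t gives 78.7%, so the normal approximation is used below.

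**3. Baseline adjustment, 2.5 read as the SD of change.** With equal variances, ANCOVA residual SD = 2.5 × √((1 + r)/2).

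| r | ANCOVA SD | n per arm for 80% | Power at 96 per arm |
|---|---|---|---|
| t-test on change | 2.50 | 99 | 79.1% |
| 0.3 | 2.02 | 64 | 93.0% |
| 0.4 | 2.09 | 69 | 91.2% |
| 0.5 | 2.17 | 74 | 89.3% |
| 0.6 | 2.24 | 79 | 87.3% |
| 0.7 | 2.30 | 84 | 85.2% |

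**4. Baseline adjustment, 2.5 read as the SD of the week-96 level.** Change SD = 2.5 × √(2(1 − r)); ANCOVA SD = 2.5 × √(1 − r²). A t-test on the level itself keeps 79.1%.

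| r | t-test on change, power at 96 | ANCOVA, power at 96 |
|---|---|---|
| 0.3 | 64.9% | 82.8% |
| 0.4 | 71.6% | 85.6% |
| 0.5 | 79.1% | 89.3% |
| 0.6 | 87.3% | 93.4% |
| 0.7 | 94.7% | 97.3% |

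**5. Strata omitted.** With balance within strata, the true SE is √(1 − R²) times the one the t-test uses, so type I error = 2 × (1 − Φ(1.96 / √(1 − R²))).

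The only figures in the document that bear on R² are in the Background: mean HbA1c 8.4% on oral drugs and 9% on insulin, in another sample. With a 50/50 split, which maximises R², and SD 2.5: R² = 0.25 × 0.6² / 2.5² = 0.09 / 6.25 = 1.4%.

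| R² | SE too large by | Type I error, t-test | Power at 96, t-test | Power at 96, strata-adjusted |
|---|---|---|---|---|
| 1.4% | 0.7% | 4.8% | not run | not run |
| 10% | 5% | 3.9% | 80.4% | 83.2% |
| 15% | 8% | 3.4% | 81.1% | 85.2% |

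A simulation of blocked randomisation in ten strata (192 patients, assumed block size 4) at R² = 10% gave a type I error of 3.9% unadjusted and 5.1% adjusted. At R² = 0 both were 5.1%.

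Steps 3 and 5 must not be added together: week-0 HbA1c may already carry much of what insulin status predicts.

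**6. Level or change under ANCOVA.** Regressing the change instead of the week-96 value on arm and week-0 HbA1c only lowers the baseline coefficient by 1. The treatment estimate and its standard error are identical.

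**The case against.** The strongest defence is that the planned test is pre-specified, valid and matched to its sample size. That stands. It also disposes of four stronger conclusions a reader might draw.

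- **That baseline HbA1c is ignored.** The criterion is defined as change from week 0 to week 96, so baseline enters by subtraction. It is only not used as a covariate with an estimated slope.
- **That the type I error is wrong in a harmful way.** The departure goes only below 5%; there is no inflation of false positives. If the strata do not predict the tested variable, there is no departure at all.
- **That the trial is underpowered at 64% to 72%.** Those figures need three conditions together: 2.5% is the SD of the level, the change is tested, and r is below 0.5. If 2.5% is the SD of change, which the order of the sample size section suggests, the t-test has 79% at 96 per arm, essentially as planned.
- **That the plan contradicts itself on the endpoint.** Under randomisation the between-arm difference in mean change and in mean week-96 HbA1c have the same expectation, so a 1% difference at two years fits either. Only the label of the SD is missing.

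The defence also has force on R². An R² of 10% to 15% has no direct support in the document; the Background figures imply about 1.4% for insulin. They concern the level of HbA1c in another sample, whereas the endpoint is change, and no centre effect is reported. The 1.4% is therefore indicative only.

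The defence does not remove the point itself. The primary method is fixed in the article, the article gives treatment heterogeneity as its reason to stratify, and adjustment had more power than the t-test in every case computed with r or R² above zero.

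**Conclusion.** The point holds as one of forgone efficiency in a valid test. The primary t-test leaves out both stratification factors and does not estimate the baseline slope.

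If 2.5% is the SD of change and the two visits have equal variances, adjusting for week-0 HbA1c takes power at 96 per arm from 79% to 93% at r = 0.3 and to 87% at r = 0.6. Omitting the strata makes the t-test conservative, with a type I error of about 4.8% at R² = 1.4% and 3.4% at R² = 15%. Both r and R² are assumptions, so the direction of the gain is firmer than its size.

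This is a worthwhile improvement at no cost in data. It is not an error that would invalidate the primary result. The unlabelled SD is a separate clarification that should be made at the same time.

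**What to change.** 1. Make the primary analysis a linear model (ANCOVA) of week-96 HbA1c, or equivalently of the change, on randomised arm, week-0 HbA1c, insulin at inclusion (yes/no) and centre (five). Report the adjusted difference with its 95% CI.
2. Keep the two-sided t-test as a supportive analysis.
3. State whether the 2.5% SD refers to the change or to the week-96 level.
4. Fix the choice before outcome data by arm are seen.

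Covariates for the GEE models and stratification of the log-rank test can be left to the statistical analysis plan.

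The cost is wording only: no new data and no additional patients. With 192 evaluable patients, residual degrees of freedom go from 192 − 2 = 190 to 192 − 8 = 184 (intercept, arm, baseline, insulin and four centre terms), which is negligible.

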### Outcomes

The main outcome is the evolution of HbA1c (%) at two years. The HbA1c will be measured by the HPLC method in a centralised laboratory (biochemistry laboratory of the Félix Guyon hospital in St Denis).

The secondary outcomes will be as follows: quarterly evolution of HbA1c (%), fasting blood glucose, anthropometric indicators (body mass index, waist circumference), blood pressure, tobacco consumption, annual screening of lipids (total cholesterol, triglycerides, HDL and LDL cholesterol), antidiabetic treatments (type and dose) and the occurrence or worsening of diabetic complications. Health practices (level of physical activity and food consumption) will be assessed by means of annual questionnaires. These have been used in Reunion Island for a number of descriptive or intervention studies: RECONSAL [50], REDIA-prev1 [51] and REDIA-prev2 [31]:

Physical activity: physical activity scores will be assessed by means of a questionnaire developed on the basis of the Baecke self-questionnaire [52], which explores professional, sporting and leisure exercise. Questions on domestic activity were added to our studies.

Food consumption: food consumption (reported energy intake, macronutrient intake, dietary habits) will be assessed by means of a rapid food frequency questionnaire relating to weekly consumption [53]. Quantities of various foods are assessed by means of a photo album. The validity of the questionnaire and the photo album for the population of Reunion was checked by comparison with food surveys.

The care and treatment courses will be assessed by means of questionnaires at inclusion and at two years, based on the questionnaire used in the French ENTRED study [54] adapted to the situation and context in Reunion and comprising 30 items.

Quality of life will be assessed annually by means of the Diabetes Quality of Life, Brief Clinical Inventory [55]. This scale, including 15 items and translated into French for Reunion, was validated for this trial among a sample of 150 Reunion’s patients presenting diabetes.

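### The primary t-test has one missing-data rule, week 84 for week 96, so randomised patients with neither value contribute nothing to it although HbA1c is collected quarterly

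*Protocol article*

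**What the plan says.** Under Statistical methods, the efficacy analysis is carried out "according to the intention to treat principles", which the article explains as "according to group allocated by randomisation". The primary test is specified "with type I error equal 5%, and bilateral formulation of Student t-test (primary analysis". The endpoint, under Sample size consideration, is "developments between inclusion (week 0) and two years (week 96".

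The only missing-data rule for that endpoint is that "the deficient data on HbA1c (%) at two years (week 96) will be replaced by the measurement obtained at week 84". Nothing is said about a patient who has neither value.

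Sample size consideration allows for an "estimated data deficiency of 20% at two years (drop out, refusals, deaths") and raises the number per group from 99 to 120.

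Under Outcomes, the secondary outcomes include "quarterly evolution of HbA1c (%), fasting blood glucose". The repeated HbA1c values are used in two further analyses under Statistical methods: the longitudinal data "will used in generalised estimating equations (GEE) adapted to repeated measurements", and a Kaplan-Meier analysis of time to HbA1c below 7%.

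**The concern.** The change from week 0 to week 96 cannot be computed for a patient with neither a week-84 nor a week-96 value, so the stated t-test cannot use that patient. Anyone who leaves before week 84 is in this position, whatever HbA1c values were recorded up to then. The primary result then describes the patients who reached week 84, not all those randomised.

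This matters if the patients who leave differ in HbA1c course from those who stay, and differ in another way in one arm than in the other. The design makes that possible. The Blinding section opens the trial after week 12. From then on, only the intervention arm has group sessions, with a reminder call before each and a follow-up call after non-attendance (Interventions). Contact with the trial is therefore unequal for about 84 of the 96 weeks. A skewed comparison of those who stay could move the estimate either way, while the values that would correct much of it are already scheduled.

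**Working it through.** **Inputs.** From Sample size consideration: difference 1%, SD 2.5%, two-sided 5%, power 80%, 99 evaluable and 120 randomised per group, 20% missing at two years. From Statistical methods: week 84 replaces week 96. From Outcomes: quarterly HbA1c. The timing of losses is not given and is assumed below.

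**1. The plan's own figure.** n per group = 2 × (1.960 + 0.842)² × 2.5² / 1² = 98.1, rounded up to 99. It reproduces.

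**2. Expected losses.** 20% of 120 = 24 per arm, 48 in all.

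**3. What the rule can fill.** For dropout, it fills losses falling between weeks 84 and 96.

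- Even loss over weeks 0 to 96: 12/96 = 12.5%. Filled: 24 × 0.125 = 3 per arm (6 in all). Left out: 21 per arm (42 in all), and 21/120 = 17.5%.
- Constant hazard: (0.8^(84/96) − 0.8)/0.2 = 11.3%. Filled: 2.7 per arm. Left out: 21.3 (17.7%).
- Even loss over weeks 12 to 96: 12/84 = 14.3%. Filled: 3.4 per arm. Left out: 20.6 (17.1%).

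**4. Range and power.** Power = Φ(1/(2.5 × √(2/n)) − 1.96), with n analysed per arm.

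| Share of losses after week 84 | Left out per arm | Percent of arm | n analysed | Power |
|---|---|---|---|---|
| 0% | 24 | 20% | 96 | 79.1% |
| 5% | 22.8 | 19% | 97.2 | 79.6% |
| 12.5% | 21 | 17.5% | 99 | 80.4% |
| 25% | 18 | 15% | 102 | 81.5% |
| 50% | 12 | 10% | 108 | 83.6% |

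Power is not the problem.

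**5. The substituted values themselves.** If the effect grew linearly to 1.0, a week-84 value would show 84/96 = 87.5% of it, a shortfall of 0.125. In 3 of 99 patients per arm this shifts the estimate by 3/99 × 0.125 = 0.004. This is trivial; the patients left out matter more.

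**6. Size of bias.** With the same fraction left out in each arm, the size of the bias is that fraction times the between-arm difference in the gap (non-completer mean change minus completer mean change). At 17.5%, a gap difference of 0.5% HbA1c gives 0.175 × 0.5 = 0.09, and a difference of 1% gives 0.175 × 1 = 0.18.

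**7. Simulation (inputs assumed).** 1,500 trials per scenario, 120 per arm, eight quarterly visits, SD of change 2.5 at week 96, about 20% lost. Quarterly dropout follows a logistic model on the last HbA1c change. The comparator is regression imputation from all quarterly values.

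| Dropout | True difference | Week-84 rule | All visits |
|---|---|---|---|
| Unrelated to HbA1c | −1.0 | −0.99 | −0.99 |
| Related, same in both arms (log-odds 0.3 per 1%) | −1.0 | −0.98 | −1.01 |
| Intervention arm only, log-odds 0.3 | −1.0 | −1.11 | −0.99 |
| Intervention arm only, log-odds 0.6 | −1.0 | −1.26 | −1.00 |
| Intervention arm only, log-odds 0.3 | 0 | −0.15 | 0.00 |

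A separate simulation (400 runs, control arm drifting upwards, control patients with high HbA1c more likely to leave) gave −0.92 to −0.94 for a true −1.0 under the planned method, and −0.99 to −1.04 with all quarterly values. The direction reverses with the arm in which dropout is informative.

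**8. Against the planned precision.** The standard error is 2.5 × √(2/99) = 0.36. The null-case shift of 0.15 is about 0.4 standard errors, and would raise the two-sided 5% error rate to about 7%: Φ(−1.96 + 0.42) + Φ(−1.96 − 0.42) = 0.062 + 0.009.

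**The case against.** Much can be said for the plan.

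- **Intention to treat.** A reader might infer that the analysis contradicts its own label. It does not. The article defines the term only as analysis in the allocated group, and the t-test meets that definition. It simply does not cover every randomised patient.
- **Scope of the rule.** It would be wrong to say that it helps only patients lost in the last 12 weeks. It also fills the value for a patient still in follow-up who misses the week-96 sample.
- **Exclusion is inferred.** The article nowhere says that patients with neither value are dropped, and an analysis plan not shown here could add a rule. However, the article fixes both the primary test and its replacement rule, and enlarges the sample for missing data. Exclusion is the natural reading.
- **Early values are not discarded.** They serve the GEE and the time-to-event analysis. They are unused only in the primary test.
- **The GEE.** It is too absolute to say that it holds only when dropout is unrelated to HbA1c. The article gives no working correlation. For a continuous outcome with a well-specified covariance, GEE comes close to a normal-likelihood repeated-measures model. Still, it is a secondary analysis of trends and does not change the primary estimate.
- **Bias is not demonstrated.** Both arms keep quarterly medical follow-up and HbA1c is measured centrally. With non-informative or arm-equal dropout the bias is about 0.01 to 0.02. The larger figures need HbA1c-driven dropout in one arm only.

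These points limit the concern to possible bias in the primary comparison. They do not supply a rule for patients with neither value, or a reason to leave the quarterly data out of the primary estimate.

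**Conclusion.** The point holds in limited form and should be fixed. As written, the primary analysis covers only patients with a week-96 or week-84 value. On evenly spread losses about 42 of 240 (17.5%) fall outside it, and about 10% to 20% of each arm across the timings examined. This rests on the article's 20% figure, on assumed timing, and on reading the single rule as the whole rule.

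Power stays between 79% and 84%. The risk is bias of unknown direction: about 0.09 to 0.18 HbA1c points for a between-arm gap difference of 0.5% to 1%, and up to 0.26 in the most extreme scenario simulated, against a standard error of 0.36. It needs dropout that depends on HbA1c and differs by arm, which the open design and unequal contact make plausible but the document does not show. A reader should not conclude that the trial's result will be biased, only that the stated method leaves it open to a bias that data already scheduled could reduce.

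**What to change.** Make the primary estimate the week-96 difference between arms, using every scheduled quarterly central-laboratory HbA1c value, by one of two routes:

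- a likelihood-based repeated-measures model with visit as a category, arm-by-visit terms, insulin stratum and centre, and an unstructured covariance; or
- multiple imputation from the quarterly values, baseline HbA1c, insulin stratum and centre, followed by the planned comparison.

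Keep baseline HbA1c in the outcome vector or in the imputation model, so that patients with no later value are also included. Requiring a post-baseline value would again leave out some of those randomised.

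State how deaths are handled, since the article counts them among the losses and either route would otherwise project HbA1c beyond death. Keep the t-test with week-84 substitution as a sensitivity analysis. Add a delta-adjusted sensitivity analysis for data missing not at random, because both routes assume that dropout is explained by observed values. Replacing the secondary GEE is optional.

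The cost is revised wording and some programming before the unblinded analysis; no new data are needed. The downside is a model-based estimate in place of a simple difference in means.
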